## Abstract

Treatment-resistant depression (TRD), characterized by the failure to achieve symptomatic remission despite multiple pharmacotherapeutic treatments, poses a significant challenge for clinicians. Electroconvulsive therapy (ECT) is an effective but limited option due to its cognitive side effects. In this context, magnetic seizure therapy (MST) has emerged as a promising alternative, offering comparable antidepressant efficacy with better cognitive outcomes. However, the clinical outcomes and cognitive effects of MST require further investigation. This double-blinded, randomized, non-inferiority study aims to compare the efficacy, tolerability, cognitive adverse effects, and neurophysiological biomarkers of MST with bilateral ECT (BT ECT) in patients with TRD. This study will employ multimodal nuclear magnetic resonance imaging (MRI) and serum neurotrophic markers to gain insight into the neurobiological basis of seizure therapy. Additionally, neurophysiological biomarkers will be evaluated as secondary outcomes to predict the antidepressant and cognitive effects of both techniques. The study design, recruitment methods, ethical considerations, eligibility criteria, interventions, and blinding procedures are described. The expected outcomes will advance the field by offering a potential alternative to ECT with improved cognitive outcomes and a better understanding of the underlying pathophysiology of depression and antidepressant therapies.

## 1. Introduction

Depression is a prevalent global health issue, affecting more than 264 million people worldwide, according to the World Health Organization (WHO)**.** However, a significant proportion of individuals with depression do not achieve symptomatic remission even after multiple appropriate pharmacotherapeutic treatments. This condition is known as treatment-resistant depression (TRD) [1]. Managing TRD poses challenges for clinicians, as they must rule out misdiagnosis, comorbid disorders, inadequate therapeutic regimens, and non-compliance with treatment before considering additional strategies such as electroconvulsive therapy (ECT) [2].

Although ECT is an effective treatment for TRD, its cognitive side effects, such as impaired mnesic and non-mnesic abilities, limit its broader use [3]. While non-mnesic abilities impairment and anterograde amnesia generally improve within 15 days after the last ECT session, retrograde amnesia can persist for years, making it the most concerning cognitive side effect of ECT [4,5,6].

Recent years have witnessed the emergence of innovative treatments for mental disorders, including psychedelics and alternative agents. Some of these drugs, such as ketamine and dextromethorphan, target NMDA receptors and offer potential for more favorable clinical profiles. Nevertheless, further research is needed to understand their underlying mechanisms and develop effective treatments [7,8].

The lack of a clear understanding of the pathophysiology of depression and antidepressant therapies also hampers the development of neuromodulation techniques, including convulsive therapies. Although various strategies have been developed to mitigate ECT-induced cognitive effects, their results have been limited [9]. One possible explanation is that electrical stimulation diffuses throughout the brain, including deep structures crucial for memory retention, due to the high resistance offered by the skull and scalp [10].

Magnetic seizure therapy (MST) has emerged as an alternative convulsive therapy that overcomes the limitations of ECT. MST utilizes a magnetic field that encounters no resistance as it passes through the scalp and skull, enabling seizure induction without directly stimulating deeper brain structures [10]. A meta-analysis by Chen et al. [11] demonstrated that MST is as effective as ECT in terms of antidepressant efficacy, but with superior cognitive outcomes, including shorter recovery and reorientation times, as well as better performances in word recall, visual memory, and verbal fluency.

However, the clinical outcomes of MST, particularly its effects on cognitive performance, are not yet fully established [12]. Moreover, despite the availability of a more focal method of seizure induction, the therapeutic targets of MST remain poorly understood, limiting the development of individualized treatments [13]. To address these gaps, we propose a double-blinded, randomized, non-inferiority study to investigate the efficacy, tolerability, cognitive adverse effects, and neurophysiological biomarkers of MST compared to bilateral ECT (BT ECT) in patients with TRD. The study will employ multimodal nuclear magnetic resonance imaging (MRI) and analyze serum neurotrophic markers to gain a better understanding of the neurobiological basis of seizure therapy. Additionally, neurophysiological biomarkers will be evaluated as a secondary outcome to predict the antidepressant and cognitive effects of both techniques.

In this article, we present the design and recruitment process of the study, as well as the ethical considerations and eligibility criteria. Furthermore, we describe the interventions, including anesthesia and monitoring procedures for both ECT and MST. The blinding protocol and the frequency and number of sessions are also outlined. The study aims to provide valuable insights into the comparative effectiveness and safety of MST and ECT for TRD, contributing to the development of optimized treatment approaches for this challenging condition.

## 2. Materials and Methods

This section aims to outline the methodology employed in conducting the study, offering a comprehensive overview of the steps and procedures undertaken for data collection and analysis.

### 2.1. Study Design, Setting, and Recruitment

The study involves a double-blinded, randomized, non-inferiority clinical trial [14] with two treatment arms (see Figure 1: study design) conducted at the Institute of Psychiatry, Hospital das Clínicas, São Paulo, Brazil.

Recruitment will be conducted through referrals from physicians in the ECT Service (mainly from the Institute of Psychiatry), self-referral via university community advertisements (e.g., leaflets and email), and advertisements on the website (www.sin.org.br), Google, and social media platforms such as Facebook.

After the recruitment and selection process, participants will undergo a baseline assessment, which includes medical evaluation, neuropsychological assessment, laboratory tests, and cranial MRI. They will then be divided into two groups (ECT and MST). The study will utilize a 1:1 controlled randomization model with blocks of random sizes and lengths generated through www.sealedenvelope.com.

Generally, during the acute phase of ECT, the frequency of treatment sessions varies from one to three times per week. Studies have indicated that ECT conducted twice a week shows comparable efficacy to ECT performed three times a week, while requiring a reduced number of treatments. Additionally, there appears to be greater efficacy of ECT applied three times a week compared to the weekly application schedule [15]. Regarding cognitive functioning, the more frequent the sessions, the greater the cognitive impairments [16]. Consequently, we have opted to conduct ECT or MST sessions during the active phase with a frequency of twice a week on non-consecutive days.

**Figure 1 biomedicines-11-02150-f001:**
[figure not shown]
Study design (BL ECT, bilateral electroconvulsive therapy; MST, magnetic seizure therapy; HAMD17, Hamilton Depression Rating Scale, 17 items [17]).

Initially, patients will receive a total of 12 sessions, including the first successful titration session. If the first titration session fails to induce adequate seizures, it will not be considered as part of the total number of sessions. After the 12th session, a clinical assessment will be performed. If the patient meets the criteria for remission, defined as a score of 7 or less on the 17-item Hamilton Depression Scale (HAMD17) [17], the sessions will be discontinued, and the patient will undergo a neuropsychological evaluation. If the patient does not achieve remission, they will receive an additional 6 sessions, bringing the total to 18, and will be re-evaluated and undergo a neuropsychological assessment. In this case, regardless of the response or remission, treatment will be discontinued after the 18th session. This is because evidence suggests that the number of sessions required to achieve response and/or remission typically ranges from approximately 6 to 15 sessions [18].

Following the final session, participants will undergo a comprehensive evaluation, including medical assessment, neuropsychological evaluation, laboratory tests, and cranial MRI. Finally, patients will be followed up for 6 months after completing the intervention, with re-evaluations at 3 and 6 months.

### 2.2. Ethical Considerations

The Local and National Ethics Committees approved the clinical trial study, which adheres to the Helsinki guidelines and their subsequent amendments. All recruited volunteers will undergo medical screening, during which the professional will explain the objectives, interventions, procedures, and potential risks of the trial. They will also receive a detailed consent form, and any questions will be answered. Written informed consent is required before starting the eligibility assessment, and patients can withdraw from participation at any time during the study. Patients who have an indication for ECT will be enrolled, as the risk of complications from ECT is low [16]. Patients will be closely monitored, and if their depression worsens, they will be discontinued from the study and treated accordingly. Participation may offer benefits such as psychiatric and psychological assessments, improvement in depression, standard care, and appropriate referrals. MRI safety criteria will be followed, and patients with contraindications will be excluded. The MRI is safe, and participants will not receive sedation, anesthesia, or contrast agents. Participants will receive medical feedback from a certified radiologist regarding their brain scan, which is a benefit.

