### 2.3. Eligibility Criteria

Trained psychiatrists/psychologists will review the diagnosis of depression using the Brazilian version of the Mini International Neuropsychiatric Interview 5.0.0 (MINI) [19], which was developed based on the *Diagnostic and Statistical Manual of Mental Disorders*, 4th edition (DSM-IV) and International Classification of Diseases and Related Health Problems, 10th revision (ICD-10). 

Inclusion criteria are: (a) age between 18 and 60 years; (b) diagnosis of major depressive disorder or depressive episode in bipolar disorder according to DSM-IV; (c) baseline HAMD17 score ≥17; (d) current TDR episode; (e) appropriate clinical condition for receiving ECT as assessed by a psychiatrist and an anesthesiologist; and (f) meeting transcranial magnetic stimulation (TMS) safety criteria [20]. In the definition of TRD for major depressive disorder, the utilization of a minimum of two prior treatment failures will be considered. Conversely, for TRD in bipolar depression, only one prior treatment failure will be required. In both cases, there must be confirmation of prior adequate dose and duration, based on clinical criteria evaluated using the Antidepressant Treatment History Form (ATHF) [21,22].

Exclusion criteria are: (a) pregnancy; (b) psychiatric comorbidity (except mild anxiety disorders); (c) depressive symptoms better explained by other clinical conditions or psychiatric disorders; (d) decompensated clinical and neurological conditions or serious sequelae of previous medical conditions; (e) use of psychoactive substances in the last 6 months (except nicotine); (f) use of monoamine oxidase inhibitors in the last 6 months; (g) application of ECT or another neuromodulation technique in the last 12 months; (h) contraindications for ECT or MRI; (i) relevant deviations in clinical laboratory parameters; or (j) inability to consent.

Discontinuation criteria are: (a) worsening depression; (b) development of suicidal ideation or suicide attempt; (c) withdraw consent; (d) development of (hypo)manic symptoms; (e) inability to induce seizures lasting at least 15 s after adjusting parameters and medications during the titration phase; (f) missing two consecutive treatment sessions; or (g) changes in drug treatment without the previous authorization.

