#### 2.4.3. MST

The MagVenture MagPro MST with Twincoil (Magventure, Farum, Denmark) will be used for MST sessions. The procedure will follow the same guidelines as ECT sessions regarding general anesthesia, oxygenation, motor activity monitoring, EEG, and postictal recovery. The Twin Coil will be centered over point Fz of the 10–20 system using an EEG cap to mark the correct point on the patient’s scalp.

The stimulation will be delivered with an amplitude of 100%, 100 Hz. In the first session, a titration of the convulsive threshold will be performed with a 2 s stimulus (200 pulses). If an adequate seizure is not triggered, the stimulus will be increased by two seconds (200 pulses) until a seizure is triggered or a maximum of 3 to 4 attempts is reached. If a seizure is not initiated in the first session, a new titration session will be scheduled. Medication will be reviewed and, if possible, the dose of benzodiazepines will be reduced depending on the opinion of the performing psychiatrist. The second titration session will repeat the same process as the first, with the parameters used in the last attempt. The maximum limit is set at 10 s of stimulation or until the coil temperature exceeds the safety limit. If no seizure is triggered in the second session, the patient will be excluded from the study. In subsequent sessions, the stimulus used will be 4 s (400 pulses) higher than the titration session, up to a maximum of 1000 pulses. If the patient has seizures of less than 20 s duration, the number of pulses will be increased by 200 pulses in the next session, until the seizures are effective or the limit of 1000 pulses is reached. These parameters were determined based on our previous experience [30].

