### 2.9. Statistical Analysis

Statistical analyses will be performed in R. The results will be considered statistically significant only if both conditions are met, that is, non-inferiority for the depression outcome, under unilateral *p* < 0.025, and superiority for the cognitive outcome, under *p* bilateral < 0.05. The following groups will be considered: experimental (E), corresponding to MST, and control/comparison (C), corresponding to ECT.

For the co-primary outcome depression (HAMD17), non-inferiority will be assessed by calculating the difference between the means of groups E and C and its 95% confidence interval at the end of the 12th session, which will then be compared to the NI margin (Ha: C-E < NI). Analyses will be performed on modified intent-to-treat (ITT) samples (at least 8 sessions of ECT/MST) and per-protocol (PP).

For the co-primary cognitive outcome (AMT [32]), we will perform linear hierarchical model analyses using a first-order regressive covariance structure, which includes all observed variables without the need to enter data for missing values. The dependent variable is the AMT score [32], the independent variables are time (all observations through week 6) and group. We will test the statistical significance of this interaction according to our superiority hypotheses controlled for age, years of schooling, and treatment-resistant depression (Ha: C-E < 0). Analyses will be performed on the ITT and PP sample.

The same linear hierarchical models will be used for all continuous secondary outcomes. We will assess response and sustained remission, that is, a clinical improvement of symptoms ≥50% (response) and a HAMD17 score ≤7 (remission) at a given point in the study, which will be maintained until the outcome. The trajectories of response and sustained remission between groups will be compared using Kaplan–Meier survival analysis. Response and remission will be compared considering non-inferiority margins of 20% and 15%, respectively. The choice of a 15% non-inferiority margin was based on the consideration that achieving a remission rate of 35% holds clinical relevance in this population with difficult-to-treat depression. Furthermore, this remission rate surpasses those achieved by more conventional and less invasive treatment options for TDR, such as repetitive TMS (rTMS) with an approximate remission rate of 20% [66] and antidepressants with a remission rate of 14% [1].

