## Figures and Tables

**Table 1 biomedicines-11-02150-t001:** Clinical measures.

Measure	Study Period					
	Prior to Acute Phase		Active Phase *	Follow-Up		
	Screening	Baseline		Post-Acute **	3 Months	6 Months
Inform Consent	x					
Demographics Form	x					
ABEP		x				
Medical History Form	x					
ATHF	x					
MINI	x					
QCT		x				
BPI		x				
HAMD17	x	x	x	x	x	x
MADRS		x	x	x	x	x
CGI		x	x	x	x	x
BDI-II		x	x	x	x	
DTS		x	x	x	x	x
BSI		x	x	x	x	x
WHOQOL		x		x	x	x

ABEP, Brazil Criterion of the Brazilian Association of Research Companies 2016 [33]; ATHF, Antidepressant Treatment History Form [22]; MINI, Mini International Neuropsychiatric Interview [19]; QCT, Questionnaire on Childhood Trauma [34]; BPI, Borderline Personality Inventory [35]; HAMD17, Hamilton Depression Rating Scale, 17 items [17]; MADRS, Montgomery–Asberg Scale [36]; CGI, Clinical Global Impression Severity (CGI-S) and Clinical Global Impression Improvement (CGI-I) scales (we will apply both the CGI-S and CGI-I) [37]; BDI-II, Beck Depression Inventory [38]; DTS, Depressive Thoughts Scale [39]; BSI, Beck Suicidal Ideation Scale [40]; WHOQOL, WHO quality of life questionnaire [41]; * after the 6th session; ** one week after the last session (12th or 18th, if applicable).

**Table 2 biomedicines-11-02150-t002:** Neurocognitive measures.

Domain	Measures	Study Period		
		Baseline	Post-Acute	6 Months
Estimated Intelligence Quotient (IQ)	WASI (Vocabulary, Matrix)	x	x	x
Attention/executive functioning; cognitive flexibility and cognitive processing speed	TMT (A & B) and FDT	x	x	x
Verbal and visual episodic memory	RAVLT and BVMT-R	x	x	x
Semantic memory and verbal fluency	FAS	x	x	x
Working memory	Foward and Reverse DGS (WAIS-III)	x	x	x
Cognitive Screening	MoCA	x	x	x
Autobiographical Memory	AMT	x	x	x
Prospective and Retrospective Memory	PRMQ	x	x	x

WASI, The Wechsler Abbreviated Scale of Intelligence [42]; TMT (A and B), Trail Making Test versions A and B [43]; FDT, Five Digit Test [44]; RAVLT, Rey Auditory Verbal Learning Test [45]; BVMT-R, Revised Brief Visuospatial Memory Test [46]; FAS, Verbal Fluency [47]; DGS—WAIS-III, Digit Span—The Wechsler Adult Intelligence Scale, Third Edition-III [48]; MoCA, Montreal Cognitive Assessment [49]; AMT, Autobiographical Memory Task [32]; PRMQ, Prospective and Retrospective Memory Questionnaire [50].

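### Patients removed from the study for worsening have no described later assessment, so the session-12 HAMD17 is missing even for some modified ITT patients and no post-baseline AMT exists for any of them

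*Protocol article*

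**What the plan says.** All references are to the protocol article.

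- **Leaving the study.** Section 2.2 states that "if their depression worsens, they will be discontinued from the study and treated accordingly". For MST, section 2.4.3 states: "If no seizure is triggered in the second session, the patient will be excluded from the study". Section 2.4.2 has the same rule for ECT. Titration is specific to the allocated device, so these exclusions come after randomisation.
- **Other reasons for stopping.** Section 2.3 begins its list "Discontinuation criteria are: (a) worsening depression; (b) development of suicidal ideation or suicide attempt; (c) withdraw consent; (d) development of (hypo)manic symptoms" and goes on to seizure failure at titration, two consecutive missed sessions and unauthorised drug changes. It does not say whether meeting a criterion ends treatment or study participation.
- **Visits.** Section 2.1 places a clinical assessment after session 12 and says "Following the final session, participants will undergo a comprehensive evaluation, including medical assessment, neuropsychological evaluation, laboratory tests, and cranial MRI". It then says that "patients will be followed up for 6 months after completing the intervention". Section 2.5 times follow-up from the last session, without giving a session number. The Table 1 footnote is narrower and defines the post-acute visit as "one week after the last session (12th or 18th, if applicable". During treatment, HAMD17 is scheduled once, after session 6. Table 2 schedules AMT at baseline, post-acute and 6 months only.
- **Analysis.** Section 2.9 compares mean HAMD17 between arms at the end of session 12, in "modified intent-to-treat (ITT) samples (at least 8 sessions of ECT/MST" and in per-protocol samples. AMT is analysed by a hierarchical model on observed data, in ITT and per-protocol samples.

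**The concern.** The removal rule and the analysis set do not fit together. The modified ITT set admits patients from 8 sessions on, while its endpoint is measured after 12. A patient removed for worsening in between belongs to the set, but no visit is described that could supply the endpoint.

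The gap is in data collection. A later analysis plan can change the set or the model, but it cannot recover scores that were never taken. For patients removed for worsening, the missing scores are missing because the patient did badly. If such removals are more frequent on MST, the observed MST mean is too favourable and non-inferiority is easier to declare. If they are more frequent on ECT, the error runs the other way.

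The AMT model does not remove the problem. A patient with only a baseline AMT adds nothing direct to the time-by-group contrast. The reason for the missing value (worsening depression during treatment) is not among the listed covariates.

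**Working it through.** **1. What each early stopper would have, following the text as written**

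| Patient | In modified ITT set? | HAMD17 after session 6 | HAMD17 at session 12 | Post-baseline AMT |
|---|---|---|---|---|
| Failed second titration | No | No | No | No |
| Removed for worsening before session 6 | No | No | No | No |
| Removed for worsening after session 6 or 7 | No | Scheduled | No | No |
| Removed for worsening after sessions 8 to 11 | **Yes** | Scheduled | **No** | **No** |
| Stopped under another criterion | Depends on sessions received | Depends on sessions received | Unclear | Unclear |

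The last row is unclear because section 2.3 does not say what is discontinued. Sections 2.1 and 2.5 could cover such a patient, but the Table 1 footnote does not. For HAMD17 in the modified ITT set, only the fourth row matters. Patients removed before session 8 are outside that set whatever is collected. For AMT, all of the first four rows matter if ITT means all randomised patients. If it means the modified set, only the fourth does.

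**2. The plan's own sample size**

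Inputs from section 2.10: margin 5.7, SD 9.5, one-sided alpha 0.025, power 0.80.

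n per arm = 2 × (1.960 + 0.842)² × 9.5² / 5.7² = 2 × 7.849 × 2.778 = 43.6, rounded up to 44, or 88 in total. This reproduces the stated 88. The enrolment of 100 leaves 12 places for attrition of every kind. That allowance protects precision, not against bias from outcome-dependent loss.

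**3. What a bias would do to the non-inferiority test**

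With 44 analysed per arm, SE = 9.5 × √(2/44) = 2.03.

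Let p be the share of an arm's modified ITT set removed for worsening at sessions 8 to 11. Let g be the HAMD17 gap between those patients and the ones measured. The observed mean is then too low by p × g. With a common gap, the bias towards MST is (p in MST − p in ECT) × g.

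One-sided type I error at a true difference equal to the margin = Φ(bias/SE − 1.96).

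The documents give neither p nor g. The values below are assumptions chosen to show a range.

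| Excess share on MST | Gap (points) | Bias (points) | Type I error |
|---|---|---|---|
| 0 | any | 0 | 0.025 |
| 5 percentage points | 5 | 0.25 | 0.033 |
| 10 percentage points | 5 | 0.50 | 0.043 |
| 10 percentage points | 10 | 1.00 | 0.071 |
| 20 percentage points | 10 | 2.00 | 0.165 |

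Ten percentage points of 44 is 4.4 patients and twenty is 8.8. The last row would use most of the 12 attrition places in one arm, for one reason and in one window of sessions, so it is an extreme case. An excess on ECT would reverse the sign.

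**The case against.** The strongest reply is that this is a journal article. Early-termination visits and follow-up of patients who stop are details an article may leave to the full protocol. That is fair as to silence, and the mere absence of an exit visit would not be a finding. What stands is what the article does state: worsening ends study participation, failed titration leads to exclusion from the study, and the post-acute visit belongs to session 12 or 18.

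Three stronger readings are tempting, and the documents do not support them.

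- **A reader might infer that early stoppers have no post-baseline outcome at all.** For HAMD17 this is wrong. Table 1 schedules it after session 6, so every modified ITT patient should have one. What is missing is the session-12 value, and section 2.9 describes no use of the earlier score in the primary contrast.
- **A reader might infer that every discontinuation criterion takes the patient out of the study.** This is explicit only for worsening and failed titration. For suicidality, (hypo)mania, missed sessions and drug changes the text is silent, and the final-session wording in section 2.1 can be read to include those patients. Nor do the documents show that patients with (hypo)mania would have high HAMD17 scores.
- **A reader might infer that the trial is biased in favour of MST by a known amount.** No removal rates by arm and no score gap are given. A calculation that counts all removals among the 50 randomised per arm would also overstate the effect on the modified ITT analysis, because removals before session 8 are outside that set.

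**Conclusion.** The point holds in a limited form. Followed as written, the article loses the session-12 HAMD17 of modified ITT patients removed for worsening at sessions 8 to 11. It also loses every post-baseline AMT of patients removed for worsening at any session and of failed titrations. For patients removed for worsening, the loss depends on outcome and follows from a stated rule. It touches both co-primary outcomes, and both must succeed for the trial to succeed.

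Direction and size cannot be derived from the documents. The type I error of about 0.07 for a 1-point bias assumes 44 analysed per arm, SD 9.5 and a bias towards MST. Equal shares and equal gaps in the two arms give no bias. For the remaining discontinuation criteria, the finding is only that the passages are unclear and disagree on which session anchors the post-acute visit.

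**What to change.** Reconcile sections 2.1, 2.2, 2.3, 2.4.2, 2.4.3 and 2.5 with the Table 1 footnote, so that stopping sessions is distinct from leaving the study. State for each discontinuation criterion which of the two it means.

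Patients who stop sessions early and do not withdraw consent should keep these HAMD17 and AMT assessments:

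- at exit, where feasible;
- at the planned calendar time of the session-12 and post-acute visits (12 sessions at two per week put session 12 at about week 6);
- at the existing follow-up visits.

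Record any new treatment with its start date. The Table 1 footnote should cover a last session other than the 12th or 18th. Timing by calendar is already used in this study: section 2.8 dates two of the blood collections from the start of treatment. The clinical stopping criteria do not change.

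The cost is a protocol amendment with matching consent wording, and a few extra uses of scales already in the study, for the patients who stop early. The downside is that some of these scores will reflect other treatment, which is why it must be recorded. The planned 88 and 100 patients are unaffected.
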